### Assessments

First of all, a standardized printed form will be used that will include personal data (name, age, sex, place of birth, contact telephone number, education, monthly family income, marital status, and occupation) and anthropometric data (height and weight, measured as recommended by the National Institute of Health, Heart, Lung, and Blood) [19]; diagnosis of current illness; preexisting illnesses; current or past smoking history; history of alcohol consumption and medications used; previous chemotherapy or radiotherapy; whether the current chemotherapy is neoadjuvant, adjuvant, treatment of choice, or palliative; and whether the patient is or was a practitioner of physical activity and how often they performed such activity.

The primary outcome will be assessed via frequency and intensity. Discomfort caused by the main adverse symptoms of chemotherapy (such as pain, nausea, and dry mouth) will be assessed using the Memorial Symptom Assessment Scale, Brazilian version (MSAS-BR) [20]. This scale consists of 32 symptoms that are scored by the patient according to their frequency and intensity (1-4 points, with 1 being less intense and frequent) and the discomfort (0-4, zero being no discomfort) that this symptom caused the previous week. This scale gives us a final index, which consists of the average of the 3 domains (frequency, severity, and bother) and all items, in addition to 4 subscales: Psych, which assesses psychological symptoms (with six items); Phys H, which assesses the most prevalent physical symptoms (with 12 items); Phys L, which assesses the less prevalent physical symptoms (with 14 items); and the Global Distress Index, which measures 4 psychological and 6 physical symptoms [20,21]. This scale will be applied in the initial and final assessments by an evaluator blind to which group the patient belongs.

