Other outcomes will be assessed, such as fatigue, level of patient mobility, length of hospital stay, and clinical complications. Fatigue will be assessed using the Brief Fatigue Inventory, Brazilian version. This inventory consists of 9 items that are rated from 0 to 10 on a visual numeric scale. The first question is a dichotomous question about whether the patient has felt tired or fatigued in the last 7 days. Three items refer to the severity of fatigue at the time of assessment, the usual fatigue in the last 24 hours, and the worst fatigue in the last 24 hours, where 0 represents no fatigue and 10 “the worst fatigue imaginable.” The other 6 items refer to how fatigue interfered with different aspects of the patient’s life in the last 24 hours; these items are “general activities,” “mood,” “ability to walk,” “work” (including work outside and at home and daily tasks), “relationships with other people,” and “enjoying life,” where 0 means that it does not interfere and 10 means that it interferes completely [22,23]. This inventory will be applied in the initial and final assessments by an evaluator blind to which group the patient belongs.

The level of mobility will be assessed using the De Morton Mobility Index. This scale is made up of 15 activities, where 11 are classified as 0 or 1 (incapable or capable, respectively) and 4 are classified as 0, 1, or 2 (incapable, partial, and capable, respectively). Of the 15 activities, 3 are performed in bed, 3 in a chair, 4 involve static balance, 2 involve walking, and 3 involve dynamic balance. The scale was translated and validated in Brazilian Portuguese [24,25] and ranges from a score of 0, which represents low mobility, to 100, which represents high mobility. This index will be applied by an evaluator who is blind to which group the patient belongs and will be applied in the initial and final assessments.

In addition, the total number of days of hospital stay, possible clinical complications (cardiac, pulmonary, infectious, or neurological) arising from chemotherapy treatment, and the need for transfer to the intensive care unit will be accessed through the medical records of the patient.

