### Statistical Design

The calculation to determine the sample size was carried out based on a previous randomized clinical trial that also compared the effect of aerobic training compared to usual care on the deleterious effects of chemotherapy in patients with breast cancer [11]. Our study was designed to detect a difference of 2.7 (SD 4) points in the physical fatigue score, in addition to a difference of 6.2 (SD 7) episodes of vomiting or nausea between the groups. A power of 80%, an α of 5%, and a loss to follow-up of 15% of the sample were considered. A sample of 94 patients (47 patients in each group) was estimated.

After the data collection, all analyses will be conducted following intention-to-treat principles and will be performed by a researcher who will not be involved in the study assessments and intervention.

For analyzing the effect of the intervention, after a descriptive analysis and the Shapiro-Wilk normality test with a visual analysis, the groups will be compared using a linear mixed model for fatigue, mobility, and chemotherapy-related symptoms before and after the intervention. The length of hospital stay will also be compared between groups using Kaplan-Meier survival analysis. The *χ*^2^ test will be used to compare the clinical complication rates between groups. Descriptive analysis will be used for recruitment, completion, and adherence rates and potential adverse events. The significance level will be set at 5%. For all these analyses, SPSS (version 21.0; IBM Corp) will be used.

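### The before-and-after mixed model, as ordinarily fitted, tests a difference in change; adjusting for the baseline score already collected would be more precise at almost no cost

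*Protocol article*

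**What the plan says.** In the protocol article, Statistical Design gives the whole efficacy model in one clause: "the groups will be compared using a linear mixed model for fatigue, mobility, and chemotherapy-related symptoms before and after the intervention". The Abstract repeats the before-and-after wording.

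Assessments fixes two time points per scale. For the MSAS-BR, which carries the primary outcome: "This scale will be applied in the initial and final assessments by an evaluator blind to which group the patient belongs". For the Brief Fatigue Inventory (BFI): "This inventory will be applied in the initial and final assessments". The De Morton Mobility Index (DEMMI) follows the same two-visit schedule.

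The sample size in Statistical Design was "designed to detect a difference of 2.7 (SD 4) points in the physical fatigue score" and, in addition, "a difference of 6.2 (SD 7) episodes of vomiting or nausea between the groups". The error rates and attrition are given as follows: "A power of 80%, an α of 5%, and a loss to follow-up of 15% of the sample were considered". The result is 94 patients, 47 per group.

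Randomization states that rooms of 2 to 4 beds, not individual patients, are allocated.

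The article does not state the fixed effects, how baseline enters the model, the covariance structure, the contrast that is the treatment effect, or a room term. It gives no correlation between baseline and final scores.

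**The concern.** With one value before and one after, a mixed model that gives each group its own mean at each time and tests group-by-time returns the raw difference in mean change. That is the usual way to set up a model described like this one. It subtracts the baseline in full (slope 1), whereas the efficient adjustment under equal variances uses slope rho. When rho is moderate, full subtraction adds noise and over-corrects for chance baseline differences. Allocating whole rooms can make such differences larger than individual allocation would, but the number of rooms and the intracluster correlation are not given, so this cannot be sized.

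What is at stake is precision on the primary and the main secondary scores, in a trial of 94 patients, using data that are collected anyway. Below rho 0.5 the change contrast is noisier than a comparison of final scores that ignores baseline.

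**Working it through.** **Inputs from Statistical Design.** Fatigue: difference 2.7, SD 4, so d = 2.7/4 = 0.675. Nausea or vomiting: difference 6.2, SD 7. Power 80%, alpha 5% (two-sided assumed), loss 15%, 47 per group. Evaluable per arm: 47 × 0.85 = 39.95, taken as 40.

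**Input assumed.** Rho, the baseline-to-final correlation: 0.3, 0.5 and 0.7.

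**The plan's own figure.** Per arm, n = 2(1.96 + 0.84)²/d².
- Fatigue: 35 per arm (36 with the t distribution), which after 15% loss gives 82 to 86 in total, depending on rounding and on how the loss is applied.
- Nausea or vomiting: 21 to 22 per arm, or 50 to 52 in total.

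The 94 is not reproduced at 80% power. It fits about 85% power for fatigue (40/0.85 = 47.06 per arm). That mismatch is a separate matter. It is noted here only because it explains why comparing final scores alone already has about 85% power in the illustration below.

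**Variances.** With equal variance s² at both times and independent patients, per patient:
- difference in change: 2(1 − rho)s²
- baseline-adjusted: (1 − rho²)s²
- ratio, adjusted to change: (1 + rho)/2

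| rho | change / s² | adjusted / s² | ratio | adjusted variance lower by |
|---|---|---|---|---|
| 0.3 | 1.40 | 0.91 | 0.65 | 35% |
| 0.5 | 1.00 | 0.75 | 0.75 | 25% |
| 0.7 | 0.60 | 0.51 | 0.85 | 15% |

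Simulation with 40 per arm gave ratios of 0.66, 0.74 and 0.87, close to the formula.

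**Which mixed model gives which answer.** One simulated data set (rho 0.5, standardised scores) was fitted three ways:
- Mixed model with free baseline means: interaction −0.745 (SE 0.216), identical to the raw difference in change.
- Mixed model with a common baseline mean, baseline still a response: −0.722 (SE 0.191).
- Regression of the final score on group and baseline: −0.718.

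The loss therefore comes from leaving the baseline means free, not from using a mixed model as such.

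**Illustration for fatigue.** SD 4 is read as the SD of a single score, with 40 per arm, a two-sided 5% t-test and clustering ignored. The standardised effect is 0.675/√(2(1 − rho)) for change and 0.675/√(1 − rho²) for the adjusted comparison.

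| rho | d, change | power | d, adjusted | power |
|---|---|---|---|---|
| 0.3 | 0.570 | 71% | 0.708 | 88% |
| 0.5 | 0.675 | 85% | 0.779 | 93% |
| 0.7 | 0.871 | 97% | 0.945 | 99% |

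At 40 per arm, 80% power needs d of about 0.634. Solving 0.675/√(2(1 − rho)) = 0.634 gives rho of about 0.43, so change-score power is below 80% only when rho is lower than that.

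**The case against.** The best reply is that the article does not state the model being criticised. It names neither the fixed effects nor the contrast, and a condensed article may leave those to a fuller document. A mixed model with a common baseline mean fits the same words and recovers nearly all the efficiency of covariate adjustment. This stands: a reader might infer that the plan commits itself to a difference in change, and the text does not go that far. What remains is that the comparison it does state admits two analyses of different precision, and the ordinary one is the less precise.

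A reader might also infer that the trial misses its 80% power. The documents do not support that. It needs rho below about 0.43, and it needs SD 4 to be a single-score SD, which the text does not say. If SD 4 is the SD of change, change-score power at 40 per arm is about 85% whatever rho is.

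Nor is a power loss shown for the primary outcome. The only inputs given are a fatigue score and a count of nausea or vomiting episodes; no MSAS-BR difference or SD appears.

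Finally, under randomisation the difference in change is unbiased, so this is not an error of validity. Regression on baseline alone would also drop patients who have only a baseline value, which sits poorly with the stated intention-to-treat analysis and the expected 15% loss. That is fair, and the fix allows for it.

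**Conclusion.** The point holds as an improvement in precision, not as the correction of a wrong analysis. If the model is fitted in the ordinary way, adjusting for baseline would cut the variance of the treatment effect by (1 − rho)/2: 35%, 25% or 15% at rho 0.3, 0.5 or 0.7. The gain tends to 50% as rho nears 0 and vanishes as rho nears 1.

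These figures rest on equal variances, independent patients and a correlation that the document does not give. Because rooms are randomised, the actual gain may differ. The power figures illustrate the fatigue input only and carry over neither to the MSAS-BR nor to the trial as a whole.

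**What to change.** Add one sentence to Statistical Design: for the MSAS-BR (primary), BFI and DEMMI, the treatment effect is the between-group difference at the final assessment, adjusted for the baseline score of the same instrument, with room as a random effect because rooms are the unit of randomisation.

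The adjustment can be made in either of two ways, and the sentence should say which:
- enter the baseline score as a covariate; or
- keep both time points as responses and constrain the groups to a common baseline mean. This also keeps patients who have only a baseline value.

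The cost is that sentence. No new data, visit or instrument is needed. The article reports recruitment and data collection as ongoing, so the choice should be fixed before outcomes are compared by group.

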### Procedures

During the protocol period, all patients admitted to the oncology ward who are identified and meet the eligibility criteria will be invited to participate in the study by the evaluating physiotherapist. These eligible patients will be informed about the objectives of the study and invited to sign the informed consent form. Next, the patients will be evaluated regarding anthropometric and clinical characteristics, fatigue, and mobility, as well as the occurrence, frequency, intensity, and discomfort of the main adverse effects of chemotherapy. After the initial assessment, patients will be randomized into an intervention group, which will perform aerobic exercise sessions, and a control group, which will receive a booklet with guidelines (the same booklet will be given to the patients in the intervention group). The next day, the intervention will begin. Aerobic training will be carried out from Monday to Friday while the patients are hospitalized for the chemotherapy cycle in the oncology ward. Before carrying out the day’s aerobic exercise session, the patients will be asked if they feel any type of discomfort that is related to the previous day’s training (for example, muscle or joint pain in the lower limbs). If for any reason chemotherapy is interrupted for a patient, the exercises will also be interrupted, and as soon as chemotherapy treatment is resumed, the exercise will also be resumed. The booklet will be given to the patients and explained by a trained physiotherapist. Patients will be re-evaluated on the day following the last day of the chemotherapy cycle regarding the occurrence, frequency, intensity, and discomfort of adverse effects of the treatment, as well as fatigue, mobility, and satisfaction with the proposed intervention.

After the study intervention period, patients who need it will receive routine physiotherapeutic care provided by the physiotherapy team at the hospital. The incidence of clinical complications from chemotherapy and the length of hospital stay will be assessed as outcomes until hospital discharge. All data will be collected by a blinded assessor. Additionally, data will be coded and entered into a Microsoft Excel spreadsheet and will be double-checked before analysis. A visual representation of the study design is presented in Figure 1.

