Feasibility is defined as the extent to which a new treatment can be implemented within a given environment. It will be evaluated by the following statements addressed to physiotherapists and patients included in this study: (1) “Physical exercise during chemotherapy treatment seems implementable”; (2) “Physical exercise during chemotherapy treatment seems possible to perform”; (3) “Physical exercise during chemotherapy treatment seems feasible”; and (4) “Physical exercise during chemotherapy treatment seems easy to use.”

Economic evaluation will be monitored during the hospitalization period [28]. The index year will refer to the year of data collection. The costs of the intervention used will be assumed through the estimated value of the instruments used (oximeter and cycle ergometer), as well as the booklets and the in-hospital physiotherapy sessions (using the reference fees from the Physiotherapy Council table). The assessment of health care costs corresponds to the individual’s costs to the health care system and the costs of lost productivity due to total days of hospitalization. This assessment will be carried out using cost information obtained at the hospital. The cost-effectiveness analysis will be carried out by evaluating the effects of the intervention using the MSAS-BR-16 questionnaire, while the cost-utility analysis will be measured by quality-adjusted life years (QALYs) using the quality-of-life questionnaire EQ-5D-3L [29]. Sensitivity analysis will test uncertainty in key parameters, such as selection of cost weights and statistical variation in quality-of-life scores.

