For economic evaluation, the analysis will be performed using chemotherapy-related symptoms, fatigue, and mobility as outcomes, and the cost-utility analysis will use QALYs. Missing data will be handled using multiple imputation by chained equations. Ten complete data sets will be created (efficiency loss <5%). Pooled estimates will be calculated according to the Rubin rules [33]. Average cost differences between groups will be calculated for total and disaggregated costs. Incremental cost-effectiveness and cost-utility rates will be calculated by dividing the difference in total costs by the difference in effects. Uncertainty surrounding cost differences and incremental cost-effectiveness and cost-utility ratios will be estimated using corrected and accelerated bootstrap techniques (5000 replications). The latter will be presented graphically in cost-effectiveness plans [34]. Cost-effectiveness acceptability curves will be estimated to indicate the probability of interventions being cost-effective compared to each other at different willingness-to-pay values [35]. Sensitivity analyses will be performed to assess the robustness of the results. The first sensitivity analysis will be performed from a health care perspective, and the second sensitivity analysis will be performed per protocol. The economic evaluation will be carried out using Stata (version 14; StataCorp).

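### The economic evaluation names no baseline adjustment for its cost and effect differences, so avoidable variance stays in the ratios, planes and acceptability curves

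*Protocol article*

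**What the plan says.** The economic part of Statistical Design (protocol article) is set out step by step: chained-equation imputation with ten data sets and Rubin pooling, then cost differences, ratios, a 5000-replication bootstrap, cost-effectiveness planes, acceptability curves and two sensitivity analyses, all in Stata.

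- **Costs:** "Average cost differences between groups will be calculated for total and disaggregated costs".
- **Ratios:** "Incremental cost-effectiveness and cost-utility rates will be calculated by dividing the difference in total costs by the difference in effects".
- **Effects:** "the analysis will be performed using chemotherapy-related symptoms, fatigue, and mobility as outcomes, and the cost-utility analysis will use QALYs".

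Neither sensitivity analysis concerns baseline adjustment; one changes the perspective and the other is per protocol.

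The clinical analysis earlier in the same section is separate and runs in SPSS: "the groups will be compared using a linear mixed model for fatigue, mobility, and chemotherapy-related symptoms before and after the intervention". It covers three of the four economic effects. QALYs are not among its outcomes.

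On measurement, Assessments says of the symptom scale: "This scale will be applied in the initial and final assessments by an evaluator blind to which group the patient belongs". It says the same in substance of the fatigue and mobility scales. For utility it says only that "the cost-utility analysis will be measured by quality-adjusted life years (QALYs) using the quality-of-life questionnaire EQ-5D-3L", and on follow-up that "Economic evaluation will be monitored during the hospitalization period". Procedures lists the first assessment thus, its closing terms referring to chemotherapy symptoms: "the patients will be evaluated regarding anthropometric and clinical characteristics, fatigue, and mobility, as well as the occurrence, frequency, intensity, and discomfort". The EQ-5D-3L is in neither that list nor the list for the final assessment.

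**The concern.** Cost-effectiveness is a stated objective and part of the hypothesis. The text describes its estimator in some detail, and at that level of detail it contains no regression and no baseline score. An analyst who followed it literally would take differences between group averages.

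With about 40 analysed patients per arm, some baseline difference is to be expected. Rooms are randomised rather than patients, so the difference may be larger than under individual allocation. An unadjusted effect carries part of that difference into the denominator of every ratio and into each point of the planes and curves. The bootstrap reports the extra spread but does not remove it. For symptoms, fatigue and mobility, the baseline scores that would remove part of it are already collected.

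QALYs are the less certain case. A QALY built from a first and a last utility contains the baseline value as a component, so adjustment could gain more there. But it needs a baseline EQ-5D-3L, which the article does not say is taken.

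**Working it through.** The article gives no SD, correlation or precision figure for any economic effect, so there is no figure of the plan's own to reproduce on this point.

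**Inputs**
- Patients per arm: 47 planned with 15% loss (Statistical Design). 47 × 0.85 = 39.95, so 40.
- Correlation ρ between first and last score: not in the document. Assumed 0.3, 0.5 and 0.7.
- Equal SD σ at both times: assumed.

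**Expected chance imbalance.** The SD of the baseline difference between arms is √(2/40) = 0.224 σ under individual randomisation. Allocation by room multiplies it by the square root of a design effect. The article gives no intracluster correlation, so I do not compute that factor.

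**Case A: effect taken as the final score** (symptoms, fatigue, mobility)
- Unadjusted variance per patient: σ². Adjusted for baseline: σ²(1 − ρ²). The cut is ρ².
- A one-SD imbalance moves the unadjusted difference by ρ × 0.224 σ.

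| ρ | variance ratio | simulated ratio | cut | shift |
|---|---|---|---|---|
| 0.3 | 0.91 | 0.92 | 9% | 0.07 σ |
| 0.5 | 0.75 | 0.76 | 25% | 0.11 σ |
| 0.7 | 0.51 | 0.51 | 49% | 0.16 σ |

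The simulation used 40 per arm and 10,000 runs. The cut passes one half only when ρ exceeds about 0.71. If the effect is instead a change from baseline, the ratio of adjusted to unadjusted variance is (1 − ρ²)/[2(1 − ρ)] = (1 + ρ)/2, a cut of 35%, 25% and 15%.

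**Case B: QALY as the average of first and last utility over a common period T**
- Unadjusted: Var[T(u0 + u1)/2] = T²σ²(1 + ρ)/2.
- Adjusted for u0: T²σ²(1 − ρ²)/4.
- Ratio: (1 − ρ²)/4 ÷ (1 + ρ)/2 = (1 − ρ)/2.

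| ρ | variance ratio | simulated ratio | cut |
|---|---|---|---|
| 0.3 | 0.35 | 0.354 | 65% |
| 0.5 | 0.25 | 0.253 | 75% |
| 0.7 | 0.15 | 0.148 | 85% |

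**Case C: QALY accrued over a stay of variable length.** Every input here is an assumption: mean utility 0.7, SD 0.2, ρ = 0.5, mean stay scaled to 1 with coefficient of variation c, and stay independent of utility.
- Variance of average utility: 0.04 × 1.5/2 = 0.03.
- Variance of stay × average utility: 0.03 + (0.49 + 0.03)c². This is 0.160 at c = 0.5 and 0.077 at c = 0.3.
- Part explained by baseline utility: (0.04 × 1.5/2)²/0.04 = 0.0225.
- Cut: 0.0225/0.160 = 14%, and 0.0225/0.077 = 29%.

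The QALY gain therefore depends on a construction that the article does not give.

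**The case against.** The strongest reply is that the ratio sentence merely defines an incremental ratio. It fits adjusted differences as well as crude ones, and the word unadjusted does not appear. Covariates for an economic regression are also the kind of detail that an article may leave to the full analysis plan. This stands in part: the article does not declare an unadjusted analysis, and the point should not be put as though it did. But a text that gives the number of imputations, the bootstrap method and the software has described its estimator, and it is reasonable to ask that the baseline term be stated there too.

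A second reply is that the clinical mixed model already uses the before and after values of three of the four effects and may supply them. It may, but the article does not say so. The economic evaluation has its own software and its own imputed and bootstrapped data, and QALYs are outside that model in any case.

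A reader might infer more: that most of the precision of the QALY difference is lost. The document does not support that without conditions. It requires a baseline EQ-5D-3L, a QALY averaging first and last utility, and a common period. None of these is stated, and economic follow-up over the hospital stay, itself an outcome, argues against the last. Nor can the loss be put as power for QALYs. The only effect sizes in the plan are for fatigue and for vomiting or nausea, and the article claims no power and plans no test for QALYs.

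**Conclusion.** The point holds as an avoidable loss of efficiency, not as an error. Under randomisation, chance imbalance adds variance and does not bias the differences in expectation; the bootstrap would show it as wider uncertainty. A reading that the ratios are invalid is not supported, and cost-effectiveness is not the primary outcome.

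The size differs by effect. The firmer part is symptoms, fatigue and mobility, where the baseline scores exist: a variance cut of 9% to 49% if effects are final scores, on the assumed ρ of 0.3 to 0.7. For QALYs, 65% to 85% applies only under the first-and-last average over a common period; with variable stay, the illustration gives about 14% to 29%. All these figures assume equal SDs at both times and individual allocation. Room allocation may make the imbalance larger, by an amount that cannot be computed from the article.

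**What to change.** In the economic part of Statistical Design, state that cost and effect differences are estimated by regression (for example seemingly unrelated regressions) within each imputed and bootstrapped data set. Adjust symptoms, fatigue and mobility for their own baseline scores and QALYs for baseline EQ-5D-3L utility. Use these adjusted differences in the ratios, planes and acceptability curves.

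In Assessments and Procedures, state that the EQ-5D-3L is given at the initial and final assessments. In the economic section, state how QALYs are built from it and over what period.

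The cost is wording and one regression step in Stata. If the EQ-5D-3L is not already given at baseline, it also adds one short questionnaire per patient. The article reports that recruitment is under way, so this last item is the urgent one: a baseline utility that was not asked for cannot be collected afterwards.
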